## 2. Materials and Methods

### 2.1. Study Design

The design is a double-blind randomized controlled trial that examines the effectiveness of a probiotic supplement, containing three Lactobacillus strains, versus placebo in a 1:1 ratio in healthy early postmenopausal women. The product will be taken daily for 12 months. This study was approved by the La Trobe University Human Research Ethics Committee (HREC 21038) and will be conducted at the Food, Nutrition and Dietetics Research Laboratory located at La Trobe University, Bundoora, Australia. The protocol was designed according to Standard Protocol Items: Recommendations for Intervention Trials (SPIRIT). Trial registration: Australia & New Zealand Clinical Trials Registry (ACTRN12621000810819).

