### 2.7. Sample Size

The sample size calculation was based on the changes observed in total tibia volumetric BMD (vBMD) between the two treatment arms (statistical power 80%, probability of type I error 0.05) and is adequate to achieve a difference of 1% (standard deviation 1.78%) in a previously published study [21]. This estimation showed the need to recruit 50 study participants per treatment arm. Expecting a drop-out rate of 20% from baseline to follow-up measurements, an additional sample of 24 study participants will be recruited, thus leading to total sample size of 124 (i.e., 62 per treatment arm).

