### 2.8. Statistical Analysis

All continuous variables will be checked for the normality of their distribution. Normally distributed variables will be presented as Mean (standard deviation), while non-normally distributed ones will be presented as Median (interquartile range). General linear models (Repeated Measures Analysis of Variance) will be used to examine within-group changes in the majority of primary and secondary outcome measures across all time points (baseline, 6-, and 12-month follow-up) separately for each group (probiotic and placebo), as well as between-group differences at each time point. Within-group changes across all time points (baseline, versus post-intervention, versus follow-up) and between-group differences in each time-point will be also examined for biological sample data using the same statistical test. Appropriate corrections will be applied for post hoc multiple comparisons, while all analyses will be adjusted for potential confounding factors (e.g., age, body mass index, sunlight exposure, etc.). Correlations will also be used to explore the relationship between questionnaires and biological sample data.

Mediation analysis will also be conducted to examine the potential mediating role of changes in gut microbiota composition, and to examine the potential mediating role of other biological markers on the changes observed in BMD and bone metabolism indices. This will be based on a multiple regression model between the intervention, the outcome, and the potential mediators (e.g., a one of the mediation tests will assess the effect of the intervention on vBMD, examining the changes in serum concentrations of inflammatory markers as potential mediators of the intervention’s effect). The analysis will provide a % mediating effect, i.e., the % of the variability of the examined outcome explained by the examined mediating factors.

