All statistical analyses will be performed using the SPSS statistical analysis software version 29 for Windows. Both Per-Protocol (PP), and Intention-to-Treat (ITT) analyses will take place. Per-protocol analysis will compare treatment groups, including only those study participants who completed the treatment that was originally allocated to them. Adherence to the intervention will also be taken into consideration in the per-protocol analysis by identifying and excluding potential non-adherent study participants from the analysis. All reported *p*-values will be two-tailed, while the level of statistical significance will be set at *p* < 0.05.

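### For the outcomes measured at 0, 6 and 12 months, repeated-measures ANOVA turns the promised ITT analysis into a completers' analysis unless missing values are imputed first

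*Protocol article*

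**What the plan says.** Section 2.8 of the protocol article names the model: "General linear models (Repeated Measures Analysis of Variance) will be used". It applies this to most primary and secondary outcomes, within each group over baseline, 6 and 12 months and between groups at each time point, and uses the same test for the biological samples. The software is SPSS 29. On analysis sets the section says "Both Per-Protocol (PP), and Intention-to-Treat (ITT) analyses will take place". It describes per-protocol as women who completed their allocated treatment, less the non-adherent. It does not describe ITT further, does not say which set is primary, and states no imputation or other missing-data method.

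Section 2.7 plans for loss: "Expecting a drop-out rate of 20% from baseline to follow-up measurements". Section 2.5 adds a route to it, since women who stop meeting the inclusion criteria or can no longer keep to the restrictions leave the study.

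The schedule differs by outcome (sections 2.6.1 and 2.6.3, Table 1). DXA, heel ultrasound and blood are taken at 0, 6 and 12 months. HR-pQCT, the primary outcome, is taken at 0 and 12 months only.

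**The concern.** Repeated-measures ANOVA in the SPSS general linear model reads one row per woman, with her visits as columns, and uses only complete rows. A woman with baseline and 6-month DXA but no 12-month DXA contributes nothing, and neither does one who misses only month 6. An analysis restricted in this way does not follow all randomised women, whatever it is called.

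Three things are at stake for the three-visit outcomes. Measurements already taken are thrown away. The ITT result loses part of its value as a contrast to the per-protocol result. And the estimates are biased if leaving is related to bone change in certain ways. That relation is possible under the article's own rules. Section 2.2 makes a T-score above −2.5 a condition of enrolment, and DXA is repeated at 6 months, so section 2.5 could be read as removing a woman because of her 6-month scan. The article does not say that it is applied in this way, or how many women would be affected.

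**Working it through.** **1. The plan's own sample size.** Inputs from section 2.7: difference 1%, SD 1.78% (total tibia vBMD), and "statistical power 80%, probability of type I error 0.05". Section 2.8 makes the tests two-tailed and section 2.1 sets equal allocation.

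n per arm = 2 × [SD × (1.960 + 0.842) / difference]² = 2 × (1.78 × 2.802)² = 49.7, so 50. This reproduces the plan: "This estimation showed the need to recruit 50 study participants per treatment arm". (The t-test version gives 50.7.) Inflating for 20% loss gives 100 / 0.8 = 125, close to the stated 124.

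**2. Women left in a complete-row analysis.** 124 × 0.20 = 24.8, so about 25 women are lost. 124 × 0.80 = 99.2 remain, or 49.6 per arm. Power at 49.6 per arm is 79.9% (normal) or 79.1% (t). Power is about as planned, so the issue is bias and discarded data.

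**3. Bias, by simulation.** None of the following assumptions is in the documents, apart from 62 women per arm and the SD of 1.78, which is borrowed from tibia vBMD.
- Placebo mean change: −0.75% at 6 months and −1.5% at 12 months. In the active arm, half the effect is present at 6 months and all of it at 12.
- SD of the 6-month change 1.4%; correlation of 6- and 12-month change 0.6.
- Drop-out after month 6: random (20%), or logit P = a − b(v − m)/s. Here v is the 6-month change (m = −0.5, s = 1.4) or the unseen 12-month change (m = −1.0, s = 1.78), and b = 1 or 2. The values of a are −1.6 and −2.2 (rule in both arms) or −1.55 and −1.6 (rule in placebo only, with b = 0 in the active arm). Drop-out is about 20–26%.
- Complete-case estimate: difference in mean 12-month change among completers. Likelihood-type estimate: within each arm, regress month 12 on month 6 in completers and average the prediction over all women.
- 2,000 trials per scenario. Simulation error is about 1.78 × √(2/49.6) / √2000 = 0.008.

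Estimated difference when the truth is 1.00 (b = 1 / b = 2):

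| Drop-out depends on | Complete-case | Likelihood |
|---|---|---|
| nothing (random) | 1.02 / 1.01 | 1.01 / 1.01 |
| 6-month change, both arms | 0.96 / 0.91 | 1.00 / 1.00 |
| 6-month change, placebo only | 0.79 / 0.58 | 1.00 / 0.99 |
| unseen 12-month change, both arms | 0.89 / 0.76 | 0.92 / 0.82 |
| unseen 12-month change, placebo only | 0.60 / 0.24 | 0.73 / 0.45 |

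Relative bias of the complete-case estimate for dependence on the 6-month change:
- Both arms: 1 − 0.959 = 4% to 1 − 0.913 = 9%.
- Placebo only: 1 − 0.786 = 21% to 1 − 0.576 = 42%.

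When the true difference is 0, the complete-case difference is about 0 under random drop-out or a shared rule. It is −0.22 / −0.41 if the 6-month rule holds in placebo only, and −0.38 / −0.76 if the unseen 12-month rule does.

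**4. Within-group changes.** Section 2.8 also tests these separately by arm. Under a shared 6-month rule and a true difference of 1.00, completers overstate the mean change by 0.21 / 0.33 points in placebo and 0.17 / 0.24 in the active arm. With no true difference and a shared rule, the error is about 0.2 to 0.6 points in each arm, the upper end being for dependence on the unseen 12-month change.

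**5. HR-pQCT.** With scans at 0 and 12 months only, a missed 6-month visit removes nobody. A woman without the 12-month scan has no post-baseline vBMD, so a mixed model on vBMD recovers little. The simulation in step 3 uses a 6-month value of the outcome itself, which does not exist for vBMD.

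**The case against.** The strongest reply is that only a journal article is at hand. Missing-data handling commonly sits in the SAP or full protocol, and section 4 refers to an a priori analysis plan. Repeated-measures ANOVA after imputation would fit both the named model and the ITT promise. This stands as a condition: that the ITT analysis is a completers' analysis is an inference that holds only if nothing is imputed. It does not remove the point, because the method that the article does fix cannot use partial records and a better one exists for the same data.

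Second, loss is already planned for and power holds at about 79–80%. That is correct, and no sample-size error is claimed.

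Third, the trial is double-blind with matched capsules, and nothing in the article says that women are told their 6-month bone results. Drop-out that follows bone change in one arm only is therefore an unfavourable scenario, and the milder shared-rule figures must stand beside it.

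A reader might go further in two ways that the documents do not support:
- That the primary vBMD analysis drops everyone with a missed visit, or carries the simulated bias. The HR-pQCT schedule rules out the first. The second would need a 6-month vBMD that is never measured.
- That the ITT and per-protocol sets would be nearly the same women. Per-protocol also excludes the non-adherent, and their number is unknown.

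**Conclusion.** The point holds for areal BMD, heel ultrasound and blood biomarkers. Without prior imputation, the named ANOVA makes ITT a completers' analysis and discards partial data on up to about 25 of 124 women at the expected drop-out. Those who leave before month 6 have only baseline values to offer, so the recoverable information may be smaller.

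The size of the between-group bias is conditional: none under random drop-out, about 4–9% of a true 1.0-point difference under a shared dependence on 6-month change, and about 20–40% if that dependence is in one arm only. Within-group changes are biased even under a shared rule. These figures rest on the assumed correlation, drop-out slopes and means, and on an SD taken from tibia vBMD; the article gives no SD of change for DXA. In the scenarios shown, the loss falls on placebo women with more bone loss, so the bias works against the probiotic. Likelihood methods correct drop-out explained by observed 6-month values, but only partly correct drop-out driven by unseen 12-month values.

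For HR-pQCT the source of any bias is the missing 12-month scan rather than the ANOVA. How much can be recovered depends on an unknown correlation with other measurements, so none of the simulated figures should be quoted for that endpoint.

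**What to change.** - **Three-visit outcomes.** Replace repeated-measures ANOVA with a likelihood-based mixed model (SPSS MIXED) with arm-by-visit and baseline-by-visit terms and unstructured covariance, using all available visits of all randomised women.
- **Analysis sets.** Name ITT, as randomised, as primary and per-protocol as supportive.
- **HR-pQCT.** Impute missing 12-month vBMD by multiple imputation within arm, with baseline vBMD, DXA and bone turnover markers as auxiliaries, then use baseline-adjusted ANCOVA. Add one delta-adjusted sensitivity analysis for drop-out that depends on unseen values.
- **If the SAP already imputes before the ANOVA,** say so where ITT is promised, and state the assumption.

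The cost is analysis-plan wording and a few days of programming. No new data are needed, the software already named is enough, and the sample size does not change. Section 3 reports the trial as ongoing without results, so the change can be made before unblinding.

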### 2.6. Outcomes

#### 2.6.1. Bone Mineral Density Measurements

The primary outcome is the change in cortical and trabecular vBMD as measured by high resolution peripheral quantitative computed tomography (HR-pQCT, Xtreme CT; Scanco Medical, Brüttisellen Switzerland) at the distal tibia and distal radius after 12 months of intervention compared to placebo. Participants will be scanned at baseline (Time point: 0) and 12 months (Time point: 12 month) to assess changes.

Scans will be performed by a trained researcher in HR-pQCT scanning and interpretation, according to the established guidelines and manufacturer’s instructions [29]. Briefly, this involves the upper and lower limbs being positioned in anatomically formed carbon fibre casts provided by the manufacturer (to minimize limb motion during scanning). Once the limb is placed into the gantry of the scanner, a 2D scout view is obtained to select the region of interest for the 3D measurement. Using the fixed offset method, which is suitable for follow-up studies, the operator will place a reference line at the inflection point on the endplate of the distal radius or tibial plafond. The scan region begins 9.5 mm and 22.5 mm proximal to the reference line for the radius and tibia, respectively. The HR-pQCT images will be analysed with specific software developed by the manufactures. A semi-automated slice-by-slice contouring process will be utilized to identify the periosteal boundary of the bone, thereby extracting the bone region from the surrounding soft tissue. The delineation of the cortical and trabecular compartments will then be performed automatically using a filter and threshold-based algorithm.

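### Section 2.8 does not name the between-arm difference in 12-month change in vBMD, the quantity that Section 2.6.1 defines as primary and Section 2.7 powers

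*Protocol article*

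**What the plan says.** Section 2.6.1 sets the target: "The primary outcome is the change in cortical and trabecular vBMD", measured "at the distal tibia and distal radius after 12 months of intervention compared to placebo". HR-pQCT has two occasions: "Participants will be scanned at baseline (Time point: 0) and 12 months (Time point: 12 month) to assess changes". Table 1 agrees.

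Section 2.7 sizes the trial on the same kind of quantity: "The sample size calculation was based on the changes observed in total tibia volumetric BMD (vBMD) between the two treatment arms". It takes 80% power and alpha 0.05 for a difference of 1% with SD 1.78%, giving 50 per arm before drop-out.

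Section 2.8 then describes general linear models (repeated measures ANOVA) over baseline, 6 and 12 months for most primary and secondary outcomes. They are to examine within-group changes "separately for each group (probiotic and placebo), as well as between-group differences at each time point". The next sentence gives the same pair of contrasts for the biological samples. On covariates it says that "all analyses will be adjusted for potential confounding factors (e.g., age, body mass index, sunlight exposure, etc".

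Section 2.8 names no group-by-time interaction, no between-arm comparison of change and no baseline-adjusted 12-month comparison. Its mediation paragraph mentions the intervention's effect on vBMD, but as part of a mechanistic analysis.

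**The concern.** The trial asks whether vBMD changes differently on probiotic than on placebo. Two kinds of contrast are named, and neither answers that directly.

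- **Change within each arm, tested separately.** One significant arm and one non-significant arm do not show that the arms differ; two significant arms do not show that they are alike.
- **Arms compared at each visit.** At 12 months this compares levels, so stable differences between women enter the error term, which a comparison of change would remove. At baseline it tests only the play of chance in a randomised trial.

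The 80% power in Section 2.7 therefore belongs to a test that Section 2.8 does not name. In addition, the three-visit model cannot apply to HR-pQCT, which has no 6-month scan.

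**Working it through.** **Inputs from the protocol article.** Difference 1%, SD 1.78%, power 80%, alpha 0.05 and 50 per arm (Section 2.7); two-tailed tests (Section 2.8). The SD is read as that of 12-month percent change, because the calculation is said to rest on changes.

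**Input not in the document.** The between-woman SD of vBMD at 12 months, as a percentage of the mean. It is varied below from 3% to 20%.

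**Step 1: reproduce the plan's figure.**
n per arm = 2 × (1.96 + 0.8416)² × 1.78² / 1² = 2 × 7.849 × 3.168 = 49.7, so 50, as stated.
At 50 per arm, SE = 1.78 × √(2/50) = 0.356, and power = Φ(1/0.356 − 1.96) = Φ(0.849) = 80.2% (79.4% by noncentral t). The arithmetic is sound, for a between-arm test of change.

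**Step 2: compare arms on 12-month levels.**
SE = SD × √(2/50) = 0.2 × SD. Two-sided power = Φ(1/SE − 1.96) + Φ(−1/SE − 1.96). The n per arm for 80% power is 2 × 7.849 × SD².

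| Assumed SD (% of mean) | SE | Power at 50 per arm | n per arm for 80% |
|---|---|---|---|
| 3 | 0.6 | 38% | 142 |
| 5 | 1.0 | 17% | 393 |
| 10 | 2.0 | 8% | 1,570 |
| 20 | 4.0 | 6% | 6,280 |

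If covariates are in the model, read the SD as what remains after adjustment. By Step 1, the level comparison reaches 80% only if that residual SD falls to about 1.78%, which is in effect adjustment for baseline vBMD.

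**Step 3: add baseline vBMD as a covariate.**
Assuming equal SDs at both visits, 1.78² = 2 × SD² × (1 − r), so r = 1 − 1.78²/(2 × SD²), and the residual SD is SD × √(1 − r²). At SD 3%: r = 0.824, residual SD 1.70%, power 83.7%. At SD 10%: r = 0.984, residual SD 1.77%, power 80.5%. At SD 20%: r = 0.996, residual SD 1.78%, power 80.3%. The planned power is recovered across the range.

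**Step 4: separate within-arm tests when the product has no effect.**
Each arm's paired t test has 50 women and SE = 1.78/√50 = 0.252. If p is the chance that one arm is significant, the chance that exactly one is significant is 2p(1 − p).

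| Common true loss | p | Exactly one arm significant |
|---|---|---|
| 0 | 0.050 | 10% |
| 0.5% | 0.495 | 50% |
| 1.0% | 0.973 | 5% |
| 2.0% | about 1 | about 0 |

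**Step 5: the same tests with a true 1% benefit.**
The pattern of a significant placebo loss with no significant probiotic loss has probability (placebo p) × (1 − probiotic p). For placebo losses of 1.0%, 1.5% and 2.0% it is 92%, 50% and 3%. The same true benefit gives quite different patterns, depending only on the background rate of loss.

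**The case against.** The best defence is that Section 2.8 is a condensed account of one two-group repeated measures ANOVA. Such a model yields a group-by-time term as standard output, and with two visits that term is the between-arm test of change. The comparative aim is plain in Sections 1 and 2.6.1, and Section 2.8 covers only the majority of outcomes. This stands in part. A reader might infer that the trial never tests the difference in change; the document does not go that far. It does, however, speak of each group separately, give the same pair of contrasts twice and name no other test for any primary outcome. A term that the software would print is not a committed primary test.

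Other strong readings are not supported:

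- **Almost no power, as a fact.** The result depends on an SD that the document does not give. What holds at every value tried is that power is far below 80% without baseline adjustment.
- **Frequent false claims of benefit.** High discordance needs a common loss near 0.5%, which no section supports. The only loss rates given are 2–2.5% a year early after menopause (Section 1) and 1.2% areal BMD loss on placebo in a cited trial's subgroup (Section 4). Neither is tibial vBMD. At 1.2% discordance is about 0.7%, and at 2% about nil. Nor does any section say that benefit would be concluded from within-arm p-values.
- **Wrong covariates.** The list is given as examples and left open, so it does not exclude baseline vBMD or years since menopause. Sunlight exposure is recorded at three visits, but nothing says that a post-randomisation value will be used.

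An unseen analysis plan may settle model details. That does not remove the point, which concerns contrasts that the article states.

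**Conclusion.** The mismatch stands and can be read from the text: Sections 2.6.1 and 2.7 define and power a between-arm difference in 12-month change, and Section 2.8 names two other contrasts. The sample size arithmetic is not at fault.

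For the 12-month level comparison, the loss of power is from about 80% to between 38% and 6%. This assumes a between-woman SD of 3% to 20% of the mean and no baseline adjustment. For the separate within-arm tests, the chance of a misleading split when the product does nothing ranges from 50% to near nil with the common loss. With the larger losses both arms are simply significant, and the tests say nothing about the product.

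The group-by-time term may be what is meant. If so, the correction only puts that intention in writing.

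**What to change.** Replace the contrast sentence in Section 2.8 with wording to this effect:

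- The primary analysis is an ANCOVA of 12-month percent (or log) change in vBMD on treatment arm, with baseline vBMD and other covariates taken at baseline only. The result is the adjusted between-arm difference with its 95% CI.
- For HR-pQCT outcomes, the model uses baseline and 12 months only.
- For outcomes measured at 0, 6 and 12 months, the between-arm test is the group-by-time contrast at 12 months.
- Within-group changes are descriptive, and the between-group test at baseline is dropped.

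The cost is wording alone. Baseline vBMD is already scanned, and no extra participants or visits are needed. Section 3 says that the study is ongoing, and Section 2.5 keeps the blind until the analysis is complete, so the change can be recorded, dated and made without knowledge of results.

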### 2.5. Restrictions during the Study

Participants will be asked to refrain from using other products containing probiotic bacteria, maintain stable body weight during the study (defined as weight changes that do not exceed ±5 kg), be fasting overnight (10 h) before all clinic visits including baseline (water allowed, but alcohol not allowed within 24 h prior to visit), refrain from strenuous exercise (defined as greater than 70% of the maximal pulse rate for one hour or more, or 24 h prior to and during the day of each clinic visit). Caffeine consumption must be limited to five cups of coffee, or corresponding amount of other caffeine-containing products, per day throughout the study period. Participants must refrain from smoking or use of nicotine-containing products, blood or plasma donations, or using calcium or vitamin D supplements or hormonal therapy for the study duration. Participants will be instructed to maintain their current physical activity habits throughout the duration of the study, unless their healthcare providers advise them differently. Once enrolled, participants who no longer meet the inclusion criteria or who can no longer comply with the restrictions will be terminated from the study. Unblinding will not take place until after the analysis is complete, even for participants who have terminated early.

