#### 2.6.5. Body Composition and Anthropometry

Body composition will be measured using DXA (Hologic) by a trained researcher. Participants will attend all study visits fasted and at approximately the same time of day per timepoint to avoid variation. Body composition will also be measured using bioimpedance analysis (BIA) with the Tanita MC-780 analyser (Poznań, Poland). Body weight and standing height is measured by using a digital scale (Seca, Hamburg, Germany) with an accuracy of ±100 g and a commercial stadiometer (Leicester Height Measure; CMS Instruments, Oxford, UK) to the nearest 0.5 cm, respectively, while participants wear light clothing and no shoes.

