#### 2.6.6. Self-Reported Questionnaires

Data collected through questionnaires will be self-reported, unless indicated where obtained with an interview with study participants. The questionnaires, administered via REDCap, will collect information on:

Demographics: The socio-demographic questionnaire will collect information on participants’ socio-demographic characteristics, i.e., date of birth, years of education, employment status, occupation, country of birth, marital status, ethnicity, and areas of residence (Time points: 0).

Medical History: Medical and surgical history will be obtained with an interview in order to verify that the eligibility criteria are met. Any medication used during the study (concomitant medications) will be recorded in the study diary/CRF. Concomitant medications will be coded according to the WHO Anatomic Therapeutic Chemical (ATC) classification system (Time points: 0).

Fracture Risk: The Fracture Risk Assessment Tool (FRAX^®^) (online version adopted to the Australian population) [32] will be used to calculate the 10-year probability of fracture without BMD. This calculation is based on age, weight, height, alcohol consumption, history of osteoporosis, and several other risk factors. FRAX^®^ was developed by the WHO, and is managed by the University of Sheffield in the UK. (https://www.sheffield.ac.uk/FRAX/tool.aspx, accessed on 1 July 2021) (Time points: 0).

Physical Activity: The Active Australia Questionnaire (AAQ) has an acceptable validity and reliability for recording physical activity levels in Australian middle-aged women [33]. Study participants will report the frequency and duration of time in the previous week spent walking briskly, in moderate-intensity leisure time physical activities, and in vigorous-intensity physical activities (Time points: 0, 6, and 12 months).

Sunlight Exposure: Data on sunlight exposure will be collected via the use of a validated questionnaire [34] that will record information on study participants’ personal ultraviolet B (UV-B) radiation exposure (i.e., time of day, latitude, and season) and modifying factors (i.e., cloud, tree cover, surface, clothing, and sunscreen use). Data on the dose of UV-B radiation in the areas of residence of study participants will also be extracted from the online records of the Australian Radiation Protection and Nuclear Safety Agency (Time points: 0, 6, and 12 months).

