Jansson and colleagues (2018) were the only authors to identify years from menopause as part of their inclusion criteria (up to 12 years from menopause) [19]. Other authors only identified postmenopausal women and specified ages ranges for inclusion (for example, 50–72 years or 60–85 years). The period immediately following menopause has been identified as the time of greatest bone loss [4], which accounts for the higher prevalence of osteoporosis in women. This presents a novel opportunity to specifically target this timeframe for intervention. Indeed, Jansson and colleagues demonstrated that when time from menopause was limited to 12 years in the inclusion criteria, the intervention group showed less aBMD loss at lumbar spine compared to placebo. When a subgroup analysis limited year from menopause to 6 years, the probiotic group experienced less than 0.2% mean aBMD loss, whereas the placebo group reported 1.2% mean aBMD loss (*p* = 0.016). Interestingly, participants that were more than 6 years from menopause in the probiotic group experienced an improvement of 0.2% mean aBMD. This might indicate that benefits of probiotic intervention may have a role to play in the retention or improvement of bone density regardless of years from menopause. Nevertheless, the current study has limited years from menopause to 8 years, but also included a general age range (45–65 years) to further elucidate this phenomenon.

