## Figures and Tables

**Figure 1 nutrients-16-01150-f001:**
[figure not shown]
Flowchart of recruitment and enrolment process.

**Table 1 nutrients-16-01150-t001:** Overview of study data collection and timepoints.

	Screening Phase	Timepoint 0	Timepoint +6 Months	Timepoint +12 Months
Screening				
Informed consent	x	x		
Inclusion/exclusion criteria	x			
DEXA (spine or total hip)	x			
Data Collection				
Informed consent	x			
Bone density measurements				
DEXA (spine, total hip, femoral neck, forearm), QUS		x	x	x
HR-pQCT (tibia, radius)		x		x
Stool sample collection and storage (−20 °C)		x	x	x
Blood collection, processing, and storage (−80 °C)		x	x	x
Body composition				
DEXA (whole body), BIA		x	x	x
Nutritional Intake				
3-day food diary, FFQ		x	x	x
Questionnaires				
Physical activity (AAQ), Sun exposure, Quality of Life, Supplement use		x	x	x
Socio-demographics, FRAX		x		

DEXA—Dual energy X-ray absorptiometry, QUS—Quantitative Ultrasound, HR-pQCT—High Resolution peripheral Quantitative Computed Tomography, BIA—Bioimpedance Analysis, FFQ—Food Frequency Questionnaire, AAQ—Active Australia Questionnaire, FRAX—Fracture Risk Assessment Tool.

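### The between-arm comparison is stated as a difference at each time point, adjusted for an open covariate list that names neither the baseline value of the outcome nor years since menopause

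*Protocol article*

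**What the plan says.** Section 2.8 of the protocol article names the model: "General linear models (Repeated Measures Analysis of Variance) will be used to examine within-group changes in the majority of primary and secondary outcome measures". It is to be run across baseline, 6 and 12 months, within each arm, and is also to give between-arm differences at each time point. A test of the group-by-time interaction is not mentioned. The same section adds that "all analyses will be adjusted for potential confounding factors (e.g., age, body mass index, sunlight exposure, etc".

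Other sections that bear on this:

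- **Primary outcome (2.6.1).** It is the 12-month change in cortical and trabecular vBMD, scanned at 0 and 12 months only.
- **Sunlight exposure (2.6.6).** It is recorded repeatedly: "Nuclear Safety Agency (Time points: 0, 6, and 12 months". Table 1 agrees, in the row "Physical activity (AAQ), Sun exposure, Quality of Life, Supplement use".
- **BMI (2.6.5 and 2.5).** "Body weight and standing height is measured by using a digital scale", with no visits given. Women are asked to "maintain stable body weight during the study (defined as weight changes that do not exceed ±5 kg".
- **Years since menopause (2.2 and Discussion).** Eligibility requires one to eight years. The Discussion says: "The period immediately following menopause has been identified as the time of greatest bone loss".

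**The concern.** Three features of section 2.8 combine.

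1. **The contrast.** Read literally, a between-arm difference at 12 months compares 12-month levels. Women differ far more in their level of bone density than in their one-year change, so this contrast is much noisier than the change on which the trial was sized. It also implies a between-arm test at baseline, which in a randomised trial tests only chance.
2. **The named covariates.** The baseline value of the outcome would repair the first problem, and it is not named. Years since menopause, on which the article builds its case for this population, is not named either, while sunlight exposure is.
3. **The form of the list.** It is open at both ends, applies to every analysis and is not tied to baseline values. Confounding is also the wrong reason for adjusting a randomised comparison. The reason is precision, which calls for a few baseline predictors chosen beforehand.

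At stake is whether the primary analysis delivers the power that the sample size section promises.

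**Working it through.** **Inputs from the protocol article.** Section 2.7: difference 1%, SD 1.78%, power 80%, type I error 0.05, 50 per arm before drop-out. Section 2.8: two-tailed tests. The sample size is based on changes in total tibia vBMD, so 1.78% is read as an SD of change.

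**Assumption.** The article gives no correlation ρ between baseline and 12-month vBMD. The range 0.80 to 0.99 is used, with equal variances at the two visits.

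**Step 1: reproduce the plan's figure.** n per arm = 2 × 1.78² × (1.96 + 0.8416)² / 1² = 49.7, so 50. This agrees. It is an unadjusted two-sample comparison of change. Its power at 50 per arm is 80.2% by the normal formula and 79.4% with the t distribution. The t distribution is used below.

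**Step 2: the SD under each analysis.**

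- Change score: 1.78.
- Plain 12-month contrast: the SD of change equals the cross-sectional SD × √(2(1 − ρ)), so the cross-sectional SD = 1.78 / √(2(1 − ρ)).
- Baseline-adjusted: cross-sectional SD × √(1 − ρ²), which simplifies to 1.78 × √((1 + ρ)/2).

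Example at ρ = 0.90: 1.78 / √0.2 = 3.98, and 1.78 × √0.95 = 1.735.

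**Step 3: power for a 1% difference, 50 per arm.**

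| ρ (assumed) | SD, plain 12-month | Power, plain | Power, change score | SD, baseline-adjusted | Power, adjusted |
|---|---|---|---|---|---|
| 0.80 | 2.81 | 42% | 79% | 1.689 | 83% |
| 0.90 | 3.98 | 24% | 79% | 1.735 | 81% |
| 0.95 | 5.63 | 14% | 79% | 1.758 | 80% |
| 0.98 | 8.90 | 9% | 79% | 1.771 | 80% |
| 0.99 | 12.59 | 7% | 79% | 1.776 | 80% |

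With two visits, the group-by-time test of a repeated-measures ANOVA is the change-score test. Under that reading, adding baseline moves power from 79.4% to between 79.6% and 83.4%, a gain of 0 to 4 points.

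**Step 4: could the named covariates rescue the plain contrast?** To bring its SD back to 1.78, age, BMI and sunlight exposure would have to explain 1 − 2(1 − ρ) of the variance in 12-month level: 60% at ρ = 0.80, 80% at 0.90 and 98% at 0.99. Nothing in the article suggests that they would.

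**Step 5: prognostic covariates such as years since menopause.** The article gives no share of variance explained. If the baseline covariates together explain 5%, 10% or 20% of the variance of change (assumed), the SD becomes 1.78 × √(1 − R²) = 1.735, 1.689 or 1.592, and power 81%, 83% or 87%.

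**The case against.** The strongest reply is that the baseline value is already in the analysis. The primary outcome is a change, baseline is one of the time points in the repeated-measures model, and the natural test in that model is group by time. If that is the intended test, the objection stands: adding baseline then gains little, and least when the correlation is high.

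Second, a list of examples excludes nothing, and a condensed article may leave the final covariate set to a full analysis plan. This also stands. A reader might infer that the trial leaves out baseline bone density and years since menopause, or that the open list contradicts the a priori analysis plan claimed in the Discussion. The text supports neither: the variables are only unnamed, and a closed list may exist elsewhere.

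Third, a reader might infer that 6- or 12-month covariate values will be adjusted for, removing part of the treatment effect. No section says so. Sunlight exposure is the only named covariate with explicit repeat measurements, and a blinded capsule is unlikely to alter it. BMI is a more plausible route, but section 2.5 limits weight change and ends participation for women who can no longer comply.

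Fourth, a reader might infer that the open list inflates the false-positive rate. That requires choosing the covariate set by its p-value. In a null simulation with 100 women and the best p-value taken over all subsets, the type I error was 6.9% to 11.0% with three candidates and 9.5% to 13.8% with five (jointly explaining 10% or 30% of the variance, assumed), against 4.5% to 5.1% for one fixed set. These are worst cases of deliberate selection, which nothing in the article proposes, and the point does not rest on them.

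Finally, years since menopause has limits as a predictor: it is restricted to one to eight years, self-reported and dated only to the year. Its gain may be modest.

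What remains is that the only between-arm comparison section 2.8 states is a difference at each time point, and the adjustment named with it does not include the variable that this contrast most needs.

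**Conclusion.** The point holds as a recommended improvement to the stated method. As written, the between-arm contrast does not match the change on which the trial was sized. Taken literally, it has about 42% to 7% power at 50 per arm, against 79% for a change score and 83% to 80% with baseline adjustment. If the group-by-time test is meant, the gain is 0 to 4 points from the baseline value, plus whatever years since menopause adds. The documents do not settle which is meant, so the size runs from large to small.

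These figures rest on the assumed correlation of 0.80 to 0.99, equal variances at both visits, and reading 1.78% as an SD of change. They do not show that the trial is too small: its sample size reproduces, and the remedy needs no more women. Nor do they show that follow-up covariates will be used. The text leaves that open and can easily close it.

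**What to change.** In section 2.8, replace the between-arm part of the model and the adjustment clause with wording such as: *The treatment effect on vBMD at 12 months, and on each other outcome at each post-baseline visit, is estimated with the baseline value of that outcome, years since menopause, age, BMI and sunlight exposure as covariates, all measured at or before time point 0. No covariate measured after randomisation enters these models, and between-arm differences at baseline are not tested.*

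If a full analysis plan already fixes a closed baseline list, cite it and check that it includes the baseline value of the outcome and years since menopause.

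**Cost.** Slightly more than one sentence, because the baseline value moves from being a response to being a covariate in the between-arm models. The within-group summaries can stay. The mediation analysis is unaffected, since it needs post-randomisation measures by design. All the variables are already collected at screening or time point 0. The article says the study is ongoing and that unblinding follows the analysis, so the change can be made before allocation is known.
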